## Abstract

**Background:**

Listening to “patient voices” in terms of symptoms, emotional status and experiences with care, is crucial for patient empowerment in clinical practice. Despite convincing evidence that routine patient reported outcomes and experience measurements (PRMs) with rapid feed-back to oncologists can improve symptom control, patient well-being and cost effectiveness, PRMs are not commonly used in cancer care, due to barriers at various level. Part of these barriers may be overcome through electronic PRMs collection (ePRMs) integrated with the electronic medical record (EMR). The PATIENT VOICES initiative is aimed at achieving a stepwise integration of ePRMs assessment into routine cancer care. The feasibility project presented here is aimed at assessing the knowledge, use and attitudes toward PRMs in a comprehensive cancer centre; developing and assessing feasibility of a flexible system for ePRM assessment; identifying barriers to and developing strategies for implementation and integration of ePRMs clinical practice.

**Methods:**

The project has been organized into four phases: a) pre-development; b) software development and piloting; c) feasibility assessment; d) post-development. A convergent mixed method design, based on concurrent quantitative and qualitative data collection will be applied. A web-survey on health care providers (HCPs), qualitative studies on patients and HCPs (semi-structured interviews and focus groups) as well as longitudinal and cross-sectional quantitative studies will be carried out. The quantitative studies will enroll 600 patients: 200 attending out-patient clinics (physical symptom assessement), 200 attending inpatient wards (psychological distress assessment) and 200 patients followed by multidisciplinary teams (patient experience with care assessment). The Edmonton symptom assessment scale, the Distress Thermometer, and a tool adapted from existing patient reported experience with cancer care questionnaires, will be used in quantitative studies. A multi-disciplinary stakeholder team including researchers, clinicians, health informatics professionals, health system administrators and patients will be involved in the development of potentially effective implementation strategies in the post development phase.

**Discussion:**

The documentation of potential advantages and implementation barriers achieved within this feasibility project, will serve as a starting point for future and more focused interventions aimed at achieving effective ePRMs routine assessment in cancer care.

**Trial registration:**

ClinicalTrials.gov (NCT03968718) May 30th, 2019.

## Background

The recognition of the patients’ perspective as crucial in medical decision making, represents a major shift in medicine during the last decades [1]. Listening to “patient voices” in terms of symptoms, function, emotional status, satisfaction and experiences with treatment and care received, is essential for the empowerment of both patients and their caregivers to become more involved in the care process. This is particularly true for cancer, where people often face difficult decisions due to the complexity of treatment choices, tied to the life-threatening nature of the illness and to its emotional consequences.

The assessment of the patient perception of his/her health condition has been labelled differently, but the terms “Quality of Life” introduced in the 1980s, and the following “Health-related Quality of life”, were for long the most frequently used. In 2006 the U.S. Food and Drug Administration proposed to use the term PROs (Patient Reported Outcomes), later extended into PROMs (Patient Reported Outcomes Measures), to indicate “*any report of the status of a patient’s health condition that comes directly from the patient, without interpretation of the patient’s response by a clinician or anyone else”* [2]. More recently the term PREMs (Patient reported experience measures) has been introduced to indicate patients’ perceptions of their experience of the process of care, rather than outcome. PREMs can evaluate objective experiences (i.e waiting time before appointment), observations of healthcare providers’ behaviour (i.e whether or not a patient was given a due information) or satisfaction for the care received, the latter being more influenced by patient expectations and preferences [3, 4]. For sake of simplicity the terminology “patient reported measures” (PRMs) will be used to jointly indicate PROMs and PREMs in the present paper.

PRMs were initially developed to be applied in clinical research to assess efficacy and effectiveness of medical interventions, but they can also be used in clinical practice to drive medical decisions. While the use of PRMs in clinical research is fairly well established, systematic assessment in clinical practice is not widely implemented in routine care delivery [5–7] and may pose practical challenges, like the burden for healthcare providers in administering questionnaires before or during the medical encounter or the difficulty in interpreting results. Nonetheless, systematic symptom assessment in oncology practice is considered one key element of effective integration between oncology and palliative care [8] and there is now convincing evidence that routine use of PROM with rapid feed-back of results to health care providers (HCP), can improve symptom control, patient well-being, cost effectiveness as well as patient engagement and survival [5, 9–12].

Engagement in health care is related to the involvement of the patients, but also of caregivers, clinicians, and other stakeholders (such as researchers, purchasers, policy makers), recognising great relevance to multidisciplinary collaboration [13]. In particular, patient engagement can be defined as the promotion and support of the active involvement and participation of patients, recognizing them adequate decision-making role within the health care process. Recent studies showed that patients with higher levels of engagement reported better physical and psycho-social outcomes of care [14], and that stakeholder engagement was critical for successful implementation of PROMs in cancer care [15].

Advances in health information technology have promoted the development of electronic tools for the collection of PROMs and PREMs through mobile devices (ePRMs), a number of which are currently used in oncology practice [16, 17]. Such systems may help in overcoming some of the limitations mentioned above, permit distant follow-up of patients who are not hospitalized, promote data sharing among care team members and offer powerful opportunities for their integration with patient data from other sources (i.e physicians reported data from electronic medical record (EMR), laboratory data, administrative and cost data).

It has recently been highlighted that successful integration of ePROMs would require overcoming not only technological and reimbursement barriers but also operational ones like standardized methods for integrating them into the clinical workflow [7]. In order to develop effective integration plans, direct evidence on acceptability and feasibility for patients and HCPs, are needed in disease-specific patient populations and countries. Actually the full potential of EMR will not be achieved without the inclusion and integration of PROMs within the EMR itself [7, 18].

At present no standardized PRMs assessment is routinely performed at the Fondazione IRCCS Istituto Nazionale Tumori of Milano (INT) and to the best of our knowledge, no evidence has been published regarding routine PROMs assessment in oncology practice in Italy. The PATIENT VOICES project is aimed at achieving a stepwise integration of PRMs assessment into routine clinical cancer care in our Institute. The feasibility project presented here is the first step in the implementation project. It has been organized into four subsequent phases as reported in Fig. 1:
pre-developmentsoftware development and pilotingfeasibility assessmentpost-development phase.

**Fig. 1 Fig1:**
[figure not shown]
Phases of the PATIENT VOICES feasibility project

Specific aims and methods of each phase are reported in the following paragraphs.

## Aims and methods

This study protocol has been developed following a convergent mixed method design, based on a concurrent quantitative and qualitative data collection, followed by separated analysis for each method with the aim to obtain different but complementary data on the same topic [19–21] thus gaining a wider understanding of feasibility of PRMs systematic assessment. The quantitative and qualitative strands of the research are performed independently, and their results are brought together in the overall interpretation in order to corroborate and expand our collected data.

### Pre-development phase

The aims of this phase are:
To assess the attitudes of cancer patients and oncology health care providers towards the routine use of PRMs in cancer care.Two focus groups, one with patients and one with clinicians (physicians, nurses and psychologists) will be carried out to explore stakeholders needs, perceptions and attitudes to the use of standardized PRMs assessment in clinical practice.A web-survey will be administered to all physicians (medical, radiation and surgical oncologists as well as intensive care specialists), nurses and other health professionals (social workers, physiotherapists and psychologists) employed at our institution (900 to 1000 people); survey remainders will be sent to non-responders until a responder rate of at least 50% will be reached [22]. A sample size of 450 responders will allow to estimate a two-sided 95% confidence interval (CI) for the mean of continuous scores with a precision (half CI width) of 9.2% of its standard deviation [23]. In case of dichotomus response to questionnaire items (yes/no), and in the conservative hypothesis of 50% of “yes”, the precision will be of 4,6% [23]. The research team will develop an ad hoc questionnaire investigating which PRMs are used in clinical practice and in research, and what are the potential advantages and drawbacks of a systematic assessment. Potential advantages and drawbacks of electronic assessment will also be investigated. Data analysis will be mainly descriptive and stratified by professional role.To identify and analyze electronic assessment systems developed and used in cancer care.A systematic review of the medical literature will be performed in order to find out which systems have been developed for ePRM assessment in cancer care. Eligible systems will be defined as those used in clinical oncology practice settings for any cancer diagnosys (medical, radiation and surgery oncology as well as palliative care and psycho-oncology) which allow the electronic self-assessment of PRMs and summarize patients’ responses to the clinician. Papers reporting evidence from any study design (from feasibility studies to RCT of system implementation) will be considered eligible. The search will be carried out on MEDLINE and EMBASE using both text search and MeSH terms. Google Scholar and Scopus in the previous 5 years will be searched in order to cover a wider set of potentially relevant sources. A search strategy for Pubmed is reported in Table 1. Appropriately revised strategies will be developed for each database. The index of the main health informatics journals covering the previous 3 years will be hand searched. Grey literature (relevant congress abstracts, web sites and press releases) will also be examined. Experts in the field will be contacted in order to identify electronic assessment systems not yet published in the literature. The review will be registered on PROSPERO database [24] and its results will be reported following the PRISMA guidelines for systematic reviews and meta-analyses [25].Electronic systems identified will be compared exploring the technical feasibility of ePROMs integration into EMR and identifiyng technological barriers and basic system requirements for their implementation into routine clinical practice. In addition, functional (ie. configuration dashboard, data exportability, data visualization, …) as well as non-functional (ie. integration with other systems, data storage, …) specifications will be examined.

**Table 1 Tab1:** Search strategy draft to retrieve papers from PubMed

**Query number**	**Query content**
#15	**#1 AND #13 AND #14**
#14	**#6 OR #7 OR #8 OR #9 OR #10 OR #11 OR #12**
#13	**#2 OR #3 OR #4 OR #5**
#12	**Computer [tiab] OR smarphone [tiab] OR web-based OR tablet [tiab]**
#11	**eHealth [tiab] OR mhealth [tiab] OR E-Health [tiab] OR m-health [tiab]**
#10	**“Electronic Health Records”[mh]**
#9	**“Medical Records Systems, Computerized”[mh]**
#8	**“telemedicine”[mh]**
#7	**“Medical Informatics”[mh]**
#6	**“Mobile Applications”[mh]**
#5	**“patient outcome assessment”[mh] OR “patient outcome assessment”[tiab]**
#4	**“quality of life”[mh] OR “quality of life”[tiab]**
#3	**“Patient Reported Experiences”[tiab] OR “Patient Reported Experience”[tiab]**
#2	**“Patient Reported Outcomes”[tiab] OR “Patient Reported Outcome”[tiab]**
#1	**cancer [tiab] OR neoplasms [mh] OR tumour [tiab] OR oncol*[tiab] OR carcinoma*[tiab] OR malignan*[tiab]**

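### Survey reminders are tied to an overall 50% response, so about half the staff may go unheard, and the stated precision does not cover the resulting non-response error

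*Protocol article*

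**What the plan says.** All of the survey plan is in the Protocol article, section Pre-development phase.

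- **Who is invited.** "A web-survey will be administered to all physicians", together with nurses and other health professionals, "employed at our institution (900 to 1000 people"). No random sample is drawn.
- **When follow-up ends.** "survey remainders will be sent to non-responders until a responder rate of at least 50% will be reached". The threshold applies to the total, not to each role.
- **Precision.** "A sample size of 450 responders will allow to estimate a two-sided 95% confidence interval (CI) for the mean of continuous scores" with a half-width of 9.2% of the standard deviation. For a yes/no item at 50%, "the precision will be of 4,6"%.
- **Analysis.** Mainly descriptive, stratified by professional role.

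The abstract gives one aim of the project as "assessing the knowledge, use and attitudes toward PRMs in a comprehensive cancer centre". The prototype system is to be built on the results of the pre-development phase (Software development and piloting), and the stakeholder team later uses the survey results when it develops implementation strategies (Post-development phase).

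**The concern.** When every member of staff is invited, random sampling is not the main source of uncertainty about that staff. The main question is whether those who answer differ from those who do not. A rule that lets reminders end once half have answered limits the effort spent on the other half, who may be the people least engaged with patient-reported measures. This is plausible here: the Discussion says that awareness of their usefulness is lacking among providers, and the survey is itself electronic and asks about electronic assessment.

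The overall threshold adds a second problem. A large role that responds well can bring the total to 50% while smaller roles are still thinly covered, yet the results are to be read role by role.

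If use and attitudes in the centre were misjudged, the error would carry into the design of the system and the implementation plan. A half-width of 4.6 points would give no sign of it. The reminder rule governs data collection, so no later analysis could recover answers that were never sought.

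**Working it through.** **Inputs from the Pre-development phase section:** staff invited N = 900 to 1000; responders n = 450; two-sided 95% interval; response target at least 50%. **Assumed, because the document gives no value:** the gap d between the percentage of yes answers among responders and among non-responders, taken as 5 or 10 points.

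**1. The plan's own figures.**
- Mean: 1.96/√450 = 0.0924, or 9.2% of a standard deviation.
- Proportion at 50%: 1.96 × √(0.25/450) = 0.0462, or 4.6 points.

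Both reproduce. They use the formula for a random sample from a very large population.

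**2. Against a finite staff.** The finite-population correction is √((N − n)/(N − 1)).
- N = 900: √(450/899) = 0.707, giving 3.27 points and 6.5% of a standard deviation.
- N = 1000: √(550/999) = 0.742, giving 3.43 points and 6.9% of a standard deviation.

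For random error about this staff, the stated half-widths are therefore wider than needed.

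**3. Non-response bias.** Bias of the responder percentage = (1 − n/N) × d. The non-response share is 1 − 450/900 = 0.50 or 1 − 450/1000 = 0.55.

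| Assumed gap d | Bias, N = 900 | Bias, N = 1000 |
|---|---|---|
| 5 points | 2.5 | 2.75 |
| 10 points | 5.0 | 5.5 |

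The bias equals the stated half-width when d = 4.62/0.50 = 9.24 points (N = 900) or 4.62/0.55 = 8.40 points (N = 1000).

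**4. Effect on coverage.** With standard error √(0.25/450) = 2.36 points and the stated half-width, the chance that the interval contains the true staff percentage is Φ((4.62 − bias)/2.36) − Φ((−4.62 − bias)/2.36).
- d = 5: 81.4% (N = 900) and 78.5% (N = 1000), against a nominal 95%.
- d = 10: 43.6% and 35.4%.

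If both the half-width and the standard error are reduced by the finite-population correction, coverage at d = 5 is 67.7% and 65.1%. The narrower interval makes the undercoverage worse.

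**5. Limits without any assumption on the gap.** If 50% of responders say yes, the true staff percentage lies between 0.50 × 50% = 25% and 25% + 50% = 75% (N = 900), or between 0.45 × 50% = 22.5% and 22.5% + 55% = 77.5% (N = 1000).

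**6. 450 against the 50% target.** 450/900 = 50%, but 450/1000 = 45%. With 1000 invited, the 50% target means 500 responders and a half-width of 1.96 × √(0.25/500) = 4.4 points.

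**The case against.** The case for leaving the plan alone has several parts.

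- **The precision is not an error.** This stands. The figures are correct for 450 responders. A reader might infer from the missing finite-population correction that they are wrong, but the omission only makes them conservative for this staff. It is also defensible if a wider or future population of providers is meant, and the article does not state the population to which the interval refers.
- **Every such precision statement leaves out bias, and non-response analyses may be in a full protocol or analysis plan that is not shown.** This stands for the analysis, so the absence of a non-response table is not in itself a finding. It does not cover the reminder rule, which the article fixes.
- **At least 50% is a minimum.** This partly stands. Nothing says that the survey closes at 50% or that later answers are discarded, and the rule is also a commitment to keep going until half have answered. But nothing in it carries reminders past that point.
- **The gap is assumed.** This stands. A reader might infer that use and attitudes will be overestimated. The document has no data on how responders differ from non-responders, so neither the size nor the direction of the bias can be asserted.
- **Reporting by role already handles role mix.** This is true for the role-specific figures, where mix is not an issue. It does not protect pooled figures, and it does not bring in more answers from small roles.
- **The consequence is modest.** This is fair. The survey is descriptive, the main endpoints are the compliance rates in the feasibility studies, and the survey is read alongside focus groups and the literature.

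**Conclusion.** The point holds as a weakness of the data-collection rule. The survey invites everyone, but its reminders are tied to an overall 50%, so follow-up may stop with about half the staff unheard and with small roles under-represented.

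The stated half-widths of 4.6 points and 9.2% of a standard deviation are correct and cover random error only. At 450 responders the bias is 0.50 to 0.55 times the responder/non-responder gap, and a gap of about 8.4 to 9.2 points would match the whole half-width. These sizes rest on an assumed gap and on the literal reading of the reminder rule.

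The finite-population correction is not the remedy: alone it narrows the interval and leaves the bias where it was. As a minor mismatch, 450 responders meet the 50% target only if 900 people are invited.

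The change is worth making because it is cheap and must be made before the survey is run. It does not touch the trial's main endpoints.

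**What to change.** In the survey paragraph of the Pre-development phase section:

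1. Keep 50% as a minimum. Send a pre-set number of reminders to all non-responders even after 50% is reached, and continue beyond that number if 50% is not yet met. A fixed number alone could end below the target.
2. Monitor response by professional role as well as overall.
3. Weight centre-wide estimates to the known staff counts by role. This corrects role mix only, not differences between responders and non-responders within a role.
4. Compare early with late responders as an indication of non-response bias.
5. State that the quoted precision covers random error and excludes non-response error.
6. Align 450 responders with the 50% target: 450 if 900 staff are invited, 500 if 1000 are.

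The cost is a few more e-mails, staff counts by role and one extra table. The downside is a slightly longer survey period.

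### The draft PubMed string misspells 'smartphone' and has no free-text 'electronic' or ePRO term in its mandatory technology block, so as printed it can miss relevant records

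*Protocol article*

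**What the plan says.** The Protocol article, Pre-development phase, plans a systematic review of electronic assessment systems used in cancer care. Eligible systems are those used in clinical oncology settings "which allow the electronic self-assessment of PRMs and summarize patients’ responses to the clinician". On databases it says: "The search will be carried out on MEDLINE and EMBASE using both text search and MeSH terms". Revised strategies are to follow for each database.

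Table 1, captioned "Search strategy draft to retrieve papers from PubMed", gives the PubMed version. Its last line, #15, joins three blocks by AND: cancer (#1), patient-reported measures (#13) and technology (#14). Block #14 is an OR of its component lines: "6 OR #7 OR #8 OR #9 OR #10 OR #11 OR #12". Lines #6 to #10 are subject headings, among them Mobile Applications and Electronic Health Records. Only two lines search free text:

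- #11: "eHealth [tiab] OR mhealth [tiab] OR E-Health [tiab] OR m-health [tiab"
- #12: "Computer [tiab] OR smarphone [tiab] OR web-based OR tablet [tiab"

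**The concern.** Because #14 enters by AND, a record that matches nothing in #6 to #12 is lost, however well it fits the cancer and patient-reported blocks. Two features of the free-text part reduce what it can catch. One term is misspelled, so the intended word is not searched. And the word that defines eligibility, 'electronic', cannot be matched in a title or abstract. A paper that describes its subject simply as electronic patient-reported outcomes in cancer depends on having been given one of five subject headings.

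The review is meant to identify technological barriers and basic system requirements, and the prototype is built on the results of the pre-development phase. A less sensitive search weakens one input to that phase. An error left in the PubMed string may also carry over when it is adapted to other databases.

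**Working it through.** The article gives no yield or sensitivity for the search, so there is no figure to reproduce. The check is a reading of the Boolean logic.

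**Inputs (Table 1).** Line #15 is #1 AND #13 AND #14; block #14 is the OR of #6 to #12.

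- Free-text technology words as printed: computer, smarphone, web-based, tablet, and four eHealth/mHealth spellings.
- Subject headings in #6 to #10: Mobile Applications; Medical Informatics; telemedicine; Medical Records Systems, Computerized; Electronic Health Records.

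**Test.** The logic was applied to six invented records. Each contains 'cancer' (passes #1) and 'patient reported outcome' (passes #13), so only #14 decides. It was applied as printed, and again with 'smartphone' and 'electronic' added as free text.

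| Technology word in text | Listed heading | As printed | With the two words added |
|---|---|---|---|
| electronic | none | missed | retrieved |
| smartphone | none | missed | retrieved |
| electronic, tablet | none | retrieved | retrieved |
| smartphone | Mobile Applications | retrieved | retrieved |
| electronic | Electronic Health Records | retrieved | retrieved |
| computerized | none | missed | missed |

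**Reading the result.**

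1. A record is lost when two conditions hold together: its only technology word is 'smartphone' or 'electronic', and it carries none of the headings in #6 to #10.
2. A second listed word, such as 'tablet', or any one of the headings rescues it.
3. The last row shows a separate gap. 'Computer' is not truncated, so 'computerized' in the text does not match, and adding the two words does not help. `computer*[tiab]` would match it. Line #1 of the same table already truncates three of its terms.

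The records were chosen to exercise the logic. The proportion retrieved among them says nothing about how many real papers would be lost.

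**The case against.** Several points against this are sound, and they limit it.

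- **The table is labelled a draft.** The article contains other spelling slips, so 'smarphone' may be a typing error in the article and not the term that would be run. The document cannot settle this. The absence of a free-text 'electronic' term, however, is not a spelling slip.
- **A reader might infer that the block has no 'electronic' term at all.** That is wrong: #10 is the heading Electronic Health Records. Only the free-text term is missing.
- **A reader might infer that the review would miss eligible systems.** The document does not support this. The unit sought is a system. It is lost only if every paper on it escapes the PubMed string and all the other routes fail: EMBASE, Google Scholar and Scopus (previous 5 years), hand search of health informatics journals (previous 3 years), grey literature and contact with experts. These routes have limits, since two are confined to recent years and the experts are asked about unpublished systems, but failure of all of them is not shown.
- **A reader might infer that the newest smartphone and tablet systems are most at risk.** 'Tablet' is correctly spelled, Mobile Applications is a listed heading, and the date-limited sources favour recent work, so this does not follow.
- **A reader might also fault block #13 for lacking symptom and distress terms, or ask for many more technology synonyms.** Eligibility is set by patient-reported measures in general. Those additions trade precision for sensitivity and are a matter of preference.

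What stands is narrower: the printed string does not search for the word that defines eligibility, nor for 'smartphone'.

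**Conclusion.** The point holds as a minor correction to the pre-development review. Run as printed, the PubMed string fails to retrieve the class of records described in the working. That follows from Table 1 alone, assuming the string is run literally and the record has no other listed technology word. How many papers, and whether any system, would be lost overall cannot be derived from the document. The review is also only one input to the prototype, alongside the focus groups and the web-survey. The compliance endpoints, their precision and the sample size of 600 are unaffected.

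**What to change.** Before the string is run and adapted to the other databases, revise line #12:

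- replace the misspelled term with `smartphone*[tiab]`;
- add `electronic*[tiab]` and `ePRO*[tiab]`;
- truncate to `computer*[tiab]` and `tablet*[tiab]`;
- leave 'web-based' without a field tag, as now, because adding `[tiab]` would narrow it.

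The edit takes minutes. The cost is more titles to screen, mainly because 'electronic' is a common word; the AND with the cancer and patient-reported blocks limits the increase, but its size cannot be given from the document.
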